**Methods/design:**

The main objective is to assess the effectiveness of olive oil, comparing it with HOFA, to treat immobilized patients at home who are at risk of pressure ulcers. As a secondary objective, the cost-effectiveness balance of this new application with regard to the HOFA will be assessed. The study is designed as a noninferiority, triple-blinded, parallel, multi-center, randomized clinical trial. The scope of the study is the population attending primary health centers in Andalucía (Spain) in the regional areas of Malaga, Granada, Seville, and Cadiz. Immobilized patients at risk of pressure ulcers will be targeted. The target group will be treated by application of an olive-oil-based formula whereas the control group will be treated by application of HOFA to the control group. The follow-up period will be 16 weeks. The main variable will be the presence of pressure ulcers in the patient. Secondary variables include sociodemographic and clinical information, caregiver information, and whether technical support exists. Statistical analysis will include the Kolmogorov-Smirnov test, symmetry and kurtosis analysis, bivariate analysis using the Student’s t and chi-squared tests as well as the Wilcoxon and the Man-Whitney U tests, ANOVA and multivariate logistic regression analysis.

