## Methods/design

The design of this study is a noninferiority, triple-blinded, parallel, multi-center, randomized clinical trial. The blinded groups are the patients and their caregivers, nurses and the research group.

The null hypothesis of this study is that the difference in the appearance of pressure ulcers in immobilized patients at home who receive olive oil (*G*_o_), in contrast to those patients applying HOFA (*G*_h_) is higher than the delta value established at 10% (*H*_0_ = *G*_o_ − *G*_h_ > 10%), that is to say, that the lower bound of the confidence intervals includes that 10%. In the event that it is possible to reject the null hypothesis, the alternative hypothesis of this study will be that olive oil is not lower than 10%, compared with the HOFA (*H*_1_ = *G*_o_ − *G*_h_ < 10%); in other words, the lower bound of the confidence interval of the difference between both products is lower than 10%.

Two procedures will be performed: usual care and application of HOFA to the control group and usual care and application of an olive-oil composition to the target group. The main outcome will be the appearance of grade 2 pressure ulcers. The accuracy of the trial with regard to the control medicine (HOFA) is widely supported, owing to the favorable historical results of such medicine against placebo [25] as per recommendations of the International Conference of Harmonization and also because the efficiency conditions of the mentioned medicine will be met for the purpose of this trial.

The target population will be patients included in the immobilized-patients program within the nursing care at home service provided in Health Centers in Andalucía (Spain), and more specifically in the regions of Malaga, Granada, Seville, and Cadiz.

The inclusion criteria will be: patients over 18 years; not having pressure ulcers; patients supported by a family or a remunerated caregiver for the application of the treatment; diagnosed by a nurse as a ‘risk for impaired skin integrity’, by applying the Braden Scale for prediction of pressure ulcer risk, showing a high risk (score ≤ 12) or moderated risk (score 13 to 16), and; patients with nutritional status assessed according to the Mini Nutritional Assessment scale scoring 10 or less.

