### Sample selection

The directors and care service coordinators of each health center will be duly informed about the trial, and they will be asked for their availability as well as their consent to take part in the trial. Nursing staff of each health center who so desire will be able to take part, being in such case responsible for the research study implementation and follow-up in their respective health center.

Records of patients included in the nursing at home program for immobilized patients will be assessed to determine whether patients comply with the inclusion requirements. At this point, such patients will sign the informed consent form and subsequently, their details will be randomized by a computer system independent of the professional staff, which will be processed at the clinical trial control center.

To achieve a power rate of 80.00% to reject the null hypothesis (*H*_0_: the difference between proportions *p*1 and *p*2 is lower than the noninferiority bound), using a normal asymptotic analysis test (noninferiority), unilateral proportions for two independent samples, taking into account that the level of statistical significance is 5.00%, and assuming that the proportion in the reference (control) group is 45.00% and the proportion in the experimental group is 45.00% [9], the proportion of experimental units in the reference group is 50% related to the total and the noninferiority bound (delta) is 10.00%, then, it will be necessary to include 306 experimental units in the reference group and 306 units in the experimental group, totalling 612 units in the study. Taking into account that the expected withdrawal rate is 15.00%, it will be necessary to enroll 360 experimental units in the reference group and 360 units in the experimental group, totalling 720 experimental units in the trial.

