The main outcome will be the incidence of grade 2 pressure ulcers in patients during the 16-weeks of follow-up (112 days). We have selected this grade because when the patient has grade 2 pressure ulcers, prevention can no longer be carried out, and prevention is the intended outcome. We are only able to conduct this trial on intact skin, therefore it is only possible to conduct the trial when the patients have no pressure ulcer or have grade 1 pressure ulcers, when there are just erythemas. Therefore, patients who develop grade 2 pressure ulcers with breaks in the skin are excluded from the trial, as we cannot keep using the products because prevention is not useful anymore. Such patients will be treated again by the nurse who will cure the pressure ulcer, although this will be done out of the trial. When preventing the patient from developing grade 2 pressure ulcers, we are also preventing greater stages of ulcer. The 112 days of follow-up are higher than trials carried out up to now, 7 days [21], 9 days [24], and 30 days [25], which is more than enough for the appearance of pressure ulcers at any stage. The appearance of grade 2 pressure ulcers will be confirmed by the inspection of those areas where the product has been applied (sacrum, hips, and heels).

As secondary endpoints, cost measures will be applied that will allow us to assess the cost-effectiveness balance of the new product (olive-oil formula) against the HOFA-based products. As inputs of this model, the cost of each treatment will be used and defined as the number of units (NE_*ij*_) necessary to carry out 16 weeks’ treatment (112 days) multiplied by the price of one unit (*P*_*i*_ and *P*_*j*_) (the price of each unit will be achieved from the information provided by each supplier according to the market price). The number of units will be the result of dividing the treatment period (DT_*ij*_) (112 days) by the number of days (*d*_*ij*_) the recipient used, according to the dose established in the trial protocol in each branch of the treatment. The resulting amount achieved shall be rounded up, even if the whole number of units has not been fully used:

$${\mathrm{NE}}_{\mathrm{ij}}={\mathrm{DT}}_{\mathrm{ij}}/d_{\mathrm{ij}}$$

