#### Statistical analysis

Initially, a descriptive analysis of the variables included in the trial will be performed. Continuous variables will be summarized with mean, standard deviation, median, and interquartile range. Categorical variables will be shown in absolute and relative frequencies. An analysis of the normal distribution by the Kolmogorov-Smirnov test, symmetry analysis, and kurtosis will be performed.

With the aim of assessing the noninferiority of the olive oil for the prevention of pressure ulcers, a contrast of association between the appearance of pressure ulcers and the kind of treatment received (olive-oil-based cream or conventional treatment) will be carried out, by absolute and relative measures of effect sizes (complete reduction of risk, number needed to treat, relative risk, and relative reduction of risk), with their respective confidence intervals at 95%. It will be determined whether the confidence interval includes the estimated delta value from the sample or not, so as to reject or accept the null hypothesis.

A bivariate analysis will be carried out using the Student’s t and chi-squared tests according to the characteristics of the variables analyzed in the event that these are normally distributed. Otherwise, nonparametric tests will be applied, such as the Wilcoxon and Man-Whitney U tests. Likewise, analysis of variance (ANOVA) will be applied for the association of quantitative and qualitative variables in the necessary cases, as well as robust measures of central tendency in cases of homoscedasticity (which will be tested by Levene’s test) by means of the Welch and Brown-Forsythe test.

An analysis according to the Kaplan-Meier curves and log-rank test will be carried out to determine the progress of the appearance of pressure ulcers in both groups, taking into account the treatment applied, the sex, age, nutritional status, and functional degree of the patient and the caregiver’s age.

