## Discussion

Pressure ulcers are nowadays considered an important health issue causing a great economic impact by substantially increasing pharmaceutical expenditure. The total expenditure of pressure ulcer treatments amounts to 5% of annual health care expenditure and causes a higher health care burden on professional staff. This is a public health problem, which affects mainly older people, thus, this disease rate is increasing.

The acceptance of our hypothesis will provide evidence supporting the regular use of olive oil (nonoxygenated fatty acids) in the prevention of pressure ulcers in primary health care, likewise involving hospital care. Furthermore, owing to the lower price of the product, primary health care districts may consider purchasing them, owing to the reduction in health care workload for professional staff, as well as for the family caregivers, given that the incidence of pressure ulcers will be lower as well as the respective reduction in pharmaceutical expenditure.

The main limitation of the trial is that when performing the cost-effectiveness analysis, the variables on caregiver inputs may not be estimated, along with those variables regarding the expenditure derived from the patient’s suffering. Likewise, there might be a selection bias due to those patients who refuse to take part in the trial, which may involve differential baseline characteristics. For the purposes of this trial, in the analysis it will be taken into account whether there are differences among those who take part in the trial and those who do not. The same procedure will be applied for withdrawals during the follow-up period. The analysis will be carried out according to the protocol and intention to treat. In the event that the results of the two types of analysis do not match, the subgroup of patients who did not comply with the protocol will be studied, to determine the reasons before reaching a final conclusion of noninferiority.

The confusion bias derived from some variables such as age, sex, type of intervention, and nutritional status of the patient will be managed during the statistical analysis stage, by means of a multivariate analysis.

The usual application of olive-oil-based formulas may be helpful in preventing the appearance of any grade of pressure ulcer in immobilized patients, and thus, it will be a cheaper treatment and may be considered as an alternative treatment.

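### Time to ulcer is related to age, nutritional score and caregiver's age by log-rank tests only; these need the measurements cut into groups, where a Cox or weekly grouped-time model would keep them whole

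*Protocol article*

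**What the plan says.** The Statistical analysis section of the protocol article states: "An analysis according to the Kaplan-Meier curves and log-rank test will be carried out to determine the progress of the appearance of pressure ulcers" in the two groups, "taking into account the treatment applied, the sex, age, nutritional status, and functional degree of the patient", together with the caregiver's age. No Cox model or other regression for time to ulcer appears anywhere in the article.

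Other parts of the article bear on this:

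- **Form of the data.** Nutritional status is measured on a scale, and entry is limited on it: "patients with nutritional status assessed according to the Mini Nutritional Assessment scale scoring 10 or less" (Methods/design). The Sample selection section has patients assessed weekly until an ulcer appears or the 16 weeks end, and it records the caregiver's age.
- **Regression already planned.** The Abstract's methods paragraph lists "ANOVA and multivariate logistic regression analysis". The Discussion adds that confounding by variables such as age, sex, type of intervention and nutritional status "will be managed during the statistical analysis stage, by means of a multivariate analysis".
- **Primary conclusion.** It rests on the confidence interval for the difference in ulcer incidence against the 10% margin, not on the log-rank tests.

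**The concern.** The log-rank test suits treatment and sex, which are already groups. Patient age and caregiver's age are numbers, and the nutritional variable is a score whose range the entry criterion has already narrowed. To enter a log-rank test, each must be cut. Cutting treats patients on the same side of the line as alike and so discards information. The test alone also gives no effect estimate, and an unstratified log-rank test takes one factor at a time.

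What is at stake is how well the trial can describe which characteristics go with earlier ulcer onset. A factor with a moderate real effect is more likely to be missed than it need be, on data that will be collected anyway.

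**Working it through.** **1. The plan's own figure.** The Sample selection section assumes 45% with ulcers in each arm, a 10-point margin, one-sided 5% and 80% power. Per arm:

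n = (1.645 + 0.842)² × 2 × 0.45 × 0.55 / 0.10² ≈ 306, or 307 if rounded up. The plan states 306, so 612 in total. With 15% withdrawal, 306 / 0.85 = 360 per arm, as stated. The sample size reproduces and is not in question.

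**2. Expected events.** 612 × 0.45 = 275.4, about 275.

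**3. Information kept after one cut.** For a normally distributed factor cut at quantile q, the share kept is φ(z_q)² / (q(1 − q)), where φ is the standard normal density.

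| Cut at | Share kept |
|---|---|
| Median | 2/π = 0.637 |
| 70th percentile | 0.576 |
| 90th percentile | 0.342 |

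At the median, 275.4 × 0.637 ≈ 175 effective events, a loss of about 36%. Uneven cuts lose more.

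**4. Power.** With β the log hazard ratio per standard deviation (SD) and D the events, two-sided 5% power ≈ Φ(√D × β − 1.96). For a median split, D is replaced by 0.637 × D. Here √275.4 = 16.60 and √175.3 = 13.24.

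- β = 0.15 (hazard ratio 1.16). Continuous: 16.60 × 0.15 − 1.96 = 0.53, power 70%. Split: 13.24 × 0.15 − 1.96 = 0.03, power 51%.
- β = 0.20 (hazard ratio 1.22). Continuous: 16.60 × 0.20 − 1.96 = 1.36, power 91%. Split: 13.24 × 0.20 − 1.96 = 0.69, power 75%.

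Over a wider range of assumed effects, the same formula gives:

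| Hazard ratio per SD | Continuous | Median split |
|---|---|---|
| 1.10 | 35% | 24% |
| 1.15 | 64% | 46% |
| 1.20 | 86% | 68% |
| 1.25 | 96% | 84% |
| 1.30 | 99% | 94% |

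**5. Simulation check.** With 612 patients, weekly inspection and about 45% with ulcers by week 16 (2,000 runs per setting), power was 87% against 68% at a hazard ratio of 1.20, and 96% against 84% at 1.25. A separate simulation (1,000 runs each) gave 69% against 49% at 1.16, and 91% against 74% at 1.22. Both agree with the formula.

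**6. The same loss in events.** At a hazard ratio of 1.20 per SD, 80% power needs (1.96 + 0.842)² / (ln 1.20)² ≈ 236 events with the factor continuous, and 236 × π/2 ≈ 371 after a median split. About 275 are expected, which is enough for the first and too few for the second.

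**The case against.** The strongest reply is that one sentence is being read as the whole plan. A reader might infer that the trial studies these factors only one at a time and cannot separate age from nutrition. The article does not support that: the Abstract and the Discussion plan a multivariate analysis that takes age, sex, intervention and nutritional status together, and logistic regression needs no cut-points. This part of the reply stands. It does not remove the point, because that model addresses whether an ulcer occurs, not when. The Discussion's list also does not name functional degree or caregiver's age, although the list is open-ended.

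A reader might also infer that cut-points will be chosen after seeing the data, with more false positives as a result. Nothing in the article plans a search over cuts. The groupings may be fixed in a full protocol or analysis plan that is not shown, so their absence here is no error. A single cut set without sight of the outcomes keeps the nominal error rate. The loss of information remains whoever sets the cut and whenever.

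The sentence may describe onset in the two arms with stratification, rather than a search for predictors, and the trial states no prognostic aim. That is fair, but a stratified log-rank test needs the same groupings. More than two ordered groups with a trend test would lose less than a median split; the article does not say that this is intended.

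Finally, no functional scale is named, so functional degree may already be a category. That factor is therefore left out of the claim that a cut is needed.

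**Conclusion.** The point holds as an inexpensive improvement to a secondary analysis. The only time-to-ulcer method named requires patient age, caregiver's age and the nutritional score to be grouped. A median split costs about 36% of the information, or roughly 16 to 20 percentage points of power at hazard ratios of 1.16 to 1.22 per SD.

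The event count comes from the plan's own 612 patients and 45% incidence. The effect sizes and the roughly normal shape of the factors are assumptions, since the article gives neither. The entry limit on the nutritional score makes normality least certain for that factor.

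Treatment and sex need no cut. The noninferiority conclusion and the sample size are untouched.

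**What to change.** In the Statistical analysis section, keep the Kaplan-Meier curves and the log-rank test for treatment. Replace the log-rank tests on the other factors by one Cox model, or a grouped-time model since onset is known only to the week. Include treatment, sex, and baseline age, nutritional score and caregiver's age as continuous terms, with functional degree in whatever form it is recorded. Report hazard ratios with 95% confidence intervals.

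The change affects wording only and uses data already planned. The cost is that proportional hazards, and a linear effect for each continuous term, must be checked.

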For the analysis on cost-effectiveness, the effectiveness measures previously established (*U*_1_ and *U*_0_) will be obtained. The increase in cost for each option (Δ*C*_*ij*_) will be estimated, as well as the increase of effectiveness rate, when comparing the two options, the cost-efficiency ratio of each treatment and the incremental cost-effectiveness ratio of each option. These values will enable us to assess the necessary cost to increase by 1% the possibilities of success when preventing pressure ulcers in these patients by using each product.

The analysis will be carried out according to the protocol, as established for the noninferiority studies, to ensure the difference conditions between the treatments and increase the rejection conditions of the null hypothesis. Nevertheless, an analysis will be carried out that is intended to compare both analyses and assess, if the analyses differ, the subgroups of patients who did not comply with the trial protocol with the aim of identifying the possible reasons for the withdrawal from the trial, before accepting or rejecting the null hypothesis. The confidence intervals of the main result variable will be analyzed to determine whether the difference found is within the bound established for the delta value. Statistical analysis will be performed using SSPS 20 software.

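### The planned reading of the cost-effectiveness results as a cost per 1% more prevention does not fit a cheaper product assumed equally effective, where the incremental ratio is unstable

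*Protocol article*

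**What the plan says.** Under Statistical analysis, the article lists four economic outputs: the difference in cost, the difference in effectiveness, a cost-effectiveness ratio for each treatment, and the ICER. It then states how they are to be read: "These values will enable us to assess the necessary cost to increase by 1% the possibilities of success when preventing pressure ulcers". The effect measure, defined under Sample selection, is the percentage of patients in whom a pressure ulcer appears.

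The sample size, also under Sample selection, is calculated "assuming that the proportion in the reference (control) group is 45.00% and the proportion in the experimental group is 45.00"%. The Background expects olive oil to protect about as well as HOFA at a much lower price. So the scenario the trial is built for is no effect difference and a negative cost difference.

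**The concern.** An ICER is the cost difference divided by the effect difference. Reading it as the price of one more point of success presupposes a new product that costs more and works better. This trial plans for something else: a cheaper product that works about equally well.

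The denominator is then mainly sampling noise around zero. A difference of one or two patients can flip the sign of the ratio and change its size many times over. The stated reading fails on both sides of zero. If olive oil is cheaper and better, it dominates, and no price is paid for the gain. If it is cheaper and slightly worse, which is compatible with noninferiority, the ratio is a saving per point of prevention given up.

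The Discussion suggests that health districts may consider buying the product because of its lower price, so the economic summary is meant to be used.

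**Working it through.** **Inputs, all from Sample selection.** Power: "To achieve a power rate of 80.00% to reject the null hypothesis". Significance level: "the level of statistical significance is 5.00"%. One-sided test: "unilateral proportions for two independent samples". Margin: "the noninferiority bound (delta) is 10.00"%. Equal allocation. Ulcer proportion 45% in each arm. Withdrawal 15%.

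**Step 1: reproduce the stated sample size.**

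n per arm = 2 × 0.45 × 0.55 × (1.645 + 0.842)² / 0.10² = 306.04.

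This agrees with the stated "306 experimental units in the reference group and 306 units in the experimental group, totalling 612 units in the study". Allowing for withdrawals, 306 / 0.85 = 360 per arm, also as stated.

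**Step 2: distribution of the ICER's denominator on the same inputs.**

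Expected difference = 45% − 45% = 0.

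SE = √(2 × 0.45 × 0.55 / 306) = 0.0402, or 4.02 percentage points. The central 95% range is ±1.96 × 4.02 = ±7.9 points.

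From 400,000 simulated binomial trials of 306 per arm, except where noted:

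| Event, true difference 0 | Probability |
|---|---|
| Observed difference exactly 0 (ratio undefined) | 3.2% |
| Olive oil numerically better | 48.4% |
| Olive oil numerically worse | 48.4% |
| Observed difference under 1 point | 20% (normal approximation), 22% (a separate binomial simulation of 200,000 trials) |
| 95% CI for the difference includes 0 | about 95% |

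About 80% of these trials meet the 10-point criterion (one-sided 5%). Among them, 36% have olive oil numerically worse and 97% have a 95% CI for the effect difference that includes zero.

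**Step 3: effect on the ratio.** The article gives no prices, so assume a saving of 1 cost unit per patient (cost difference −1). One patient is 100/306 = 0.327 points.

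- One ulcer fewer on olive oil: ICER = −1 / 0.327 = −3.06 units per point.
- One ulcer more on olive oil: ICER = −1 / (−0.327) = +3.06 units per point.
- Equal counts: undefined.

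These nearly identical data sets give the two most extreme finite values the ratio can take under this assumption. The simulated 2.5th and 97.5th percentiles are also −3.06 and +3.06, and the quartiles are −0.34 and +0.34. The positive values are savings per point lost.

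**Step 4: if the true rates are not equal.**

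| True difference, either direction | Observed sign opposite to the true one | 95% CI includes 0 |
|---|---|---|
| 2 points | about 30% | about 92% |
| 5 points | about 10% | about 75–77% |

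**Step 5: the same data on the net-benefit scale.** INMB = λ × (difference in ulcer-free proportion) − (cost difference), where λ is willingness to pay per ulcer avoided. Going from one ulcer fewer to one ulcer more on olive oil changes INMB by λ × 2/306 = 0.0065λ. At equal counts INMB is simply the saving. It has no singularity.

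**The case against.** The strongest reply is that the ICER does not stand alone. The cost difference and the effect difference are planned outputs too, so a reader can tell cheaper and better from dearer and worse. The article also plans a 95% CI for the absolute risk difference, so the uncertainty of the denominator will be visible. If the effects are equal, the cost difference answers the economic question, and it will be estimated. All of this stands. A reader might infer that the sign cannot be interpreted at all, that the ICER is the only planned summary, or that the secondary objective will get no usable answer. The document supports none of these.

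Second, 45% in both arms is a planning input, not a forecast. The Background asks whether olive oil is less or more effective, and the Discussion speaks of a lower incidence. This also stands: the even split of signs belongs to exact equality, and even there about 97% of trials give a defined ratio. Step 4 shows, however, that the instability persists at nearby true differences.

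Third, interval methods and graphical displays for an economic analysis are commonly left to a fuller plan. Agreed, and their absence is no part of this point. The point is that the summary and reading the article does fix do not match its own assumptions.

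Fourth, net benefit adds no information on effect: its effect term has SE λ × 0.040. Product cost comes largely from a formula, so a bootstrap of cost would mainly reflect nurse visits. Both are true. The advantage is only that the summary stays defined and has a finite interval.

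**Conclusion.** The concern holds for the ratio and its stated reading. With 45% in both arms and 306 evaluable patients per arm, the denominator has mean 0 and SE 4.02 points. The ratio is undefined in about 3% of trials, and its sign is otherwise a near-even split. Reading the results as the price of 1% more success does not suit a product expected to be cheaper and about equally effective. The planned cost and effect differences identify the quadrant but do not cure either problem.

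The size rests on the planning assumption of equal rates, and the ICER illustration rests on an assumed one-unit saving. The instability weakens as the true difference grows: at 5 points the observed sign is wrong in about 10% of trials. The point should be corrected before analysis. It touches the secondary objective only; the primary noninferiority test and the sample size are unaffected.

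**What to change.** - Make the main cost-effectiveness summary the mean cost difference with its 95% CI, together with the incremental net monetary benefit and a bootstrap 95% CI over a stated range of willingness to pay per ulcer avoided.
- Show the ICER only alongside its two components, on the cost-effectiveness plane.
- Do not use the per-treatment average ratios to compare the arms, because they do not answer the incremental question.
- Replace the per-1% reading with one that covers each quadrant: dominance where olive oil is cheaper and better, and a saving per point of prevention lost where it is cheaper and worse.

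The cost is a change of analysis wording and a bootstrap on data already being collected. The one real burden is that a willingness-to-pay range must be stated, and the article currently gives none.

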## Abstract

**Background:**

Pressure ulcers are considered an important issue, mainly affecting immobilized older patients. These pressure ulcers increase the care burden for the professional health service staff as well as pharmaceutical expenditure. There are a number of studies on the effectiveness of different products used for the prevention of pressure ulcers; however, most of these studies were carried out at a hospital level, basically using hyperoxygenated fatty acids (HOFA). There are no studies focused specifically on the use of olive-oil-based products and therefore this research is intended to find the most cost-effective treatment and achieve an alternative treatment.

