As a variable cost, the number of visits of the nurse to the patient’s home during the trial period (VE_*i*_) will be used, which will act as a proxy measure of the level of care required. The mean time spent on each visit will be estimated according to the standard value of time within the community-health nurse working hours spent during a nursing care at home visit (this information will be obtained from the human resources management divisions of the different health districts and an assessment test will be carried out on the length of 30 visits to patients with the characteristics complying with the inclusion criteria, randomly selected among the health centers included in the study, prior to the commencement of the trial). Structural fixed costs will not be included, as in all cases the care assistance is provided at the patient’s home and the services are already included in the aforementioned variable. It will not be possible to assess the cost derived from the family care, since this is quite difficult to achieve and has a high variability. Therefore, this will not be included in the model. In those cases when there is a remunerated caregiver, such cost will not be included in the total costs either, as it would create a bias in the estimation when comparing them with those patients who are not assisted by a remunerated caregiver. Furthermore, the intangible costs derived from certain aspects, such as the pain level derived from the process will not be included either. Therefore, the estimation of total costs (CT) in the model will remain as follows:

$${\mathrm{CT}}_{\mathrm{ij}}={\mathrm{NE}}_{\mathrm{ij}}+{\mathrm{VE}}_{\mathrm{ij}}{}_{.}$$

The effectiveness variable will be the appearance of pressure ulcers. A limited number of states will be taken into account: appearance of pressure ulcers (*U*_1_) and nonappearance of pressure ulcers (*U*_0_). The incidence will be estimated in percentages, which will be used for the incremental estimations on cost-effectiveness.

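### The cost of raising prevention success by 1% is promised for each product, but two active arms can give it only for olive oil relative to HOFA

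*Protocol article*

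**What the plan says.** The cost-effectiveness paragraph under Statistical analysis plans four quantities. Two are differences: the increase in cost, and the change in effectiveness ("as well as the increase of effectiveness rate, when comparing the two options"). The other two are ratios: "the cost-efficiency ratio of each treatment and the incremental cost-effectiveness ratio of each option". The paragraph then interprets all of them together, with this stated purpose: "assess the necessary cost to increase by 1% the possibilities of success when preventing pressure ulcers in these patients by using each product".

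The effect measure is defined at the end of the cost model, under Sample selection. Each patient is classed as ulcer or no ulcer, and "The incidence will be estimated in percentages, which will be used for the incremental estimations on cost-effectiveness".

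Methods/design describes the two arms as "usual care and application of HOFA to the control group and usual care and application of an olive-oil composition to the target group". There is no arm with usual care alone.

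**The concern.** A cost per added 1% of success is a marginal quantity. It needs a reference level of success from which the gain is counted. For a single product, the natural reference is usual care without that product, and this trial does not observe it.

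The trial does observe a contrast between olive oil and HOFA, and that contrast gives one incremental ratio. It does not give one for each option, and it is not a figure for each product. The only listed quantity that comes once per product and fits the wording is the arm's own cost divided by its own ulcer-free percentage. That ratio contains no contrast, and it credits every ulcer-free patient to the product, including those who would have stayed ulcer-free anyway.

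Cost-effectiveness is the declared secondary objective. At stake is a reported figure per product that carries a marginal meaning the design cannot support.

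**Working it through.** **Inputs.** The planning proportion is 45% in both arms, the margin is 10 points, one-sided significance is 5% and power is 80% (Sample selection). There are two active arms (Methods/design). The protocol gives no prices, no mean costs and no ulcer-free rate without a product. Those values below are assumptions.

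**The plan's own figure.** It states no cost-effectiveness figure, so the check is on the sample size that carries the 45%. n per arm = 2 × 0.45 × 0.55 × (1.645 + 0.842)² / 0.10² = 306.04, against 306 stated. Allowing for withdrawal, 306 / 0.85 = 360, as stated. The 45% is therefore the value actually used. Because 0.45 × 0.55 is the same either way, the sample size does not show whether 45% is the ulcer rate or the ulcer-free rate. I take it as the ulcer rate, so the ulcer-free percentage is S = 55.

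**What each ratio contains.** C is mean cost per patient in an arm, and U is the ulcer-free percentage without a product.

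- Average ratio of one arm: C / S. Neither U nor the other arm enters.
- Incremental ratio of the trial: (C_olive − C_HOFA) / (S_olive − S_HOFA). There is one value for two arms. At the planned equal proportions its denominator is 0.
- Cost per added point for one product: (cost added by the product) / (S − U). U is not observed.

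**A product that adds nothing.** Take C = 100 units, all of it added by the product. With S = U = 55 the average ratio is 100 / 55 = 1.82 units per point, while the cost per added point is 100 / 0, which is undefined. With a background of 45, 55, 70 or 90%, the average ratio for such a product is 2.22, 1.82, 1.43 or 1.11. It improves as the background improves, with no contribution from the product. Conversely, with S held at 55 and true gains of 1, 5, 10 or 20 points, the cost per added point is 100, 20, 10 or 5 units, while the average ratio stays at 1.82.

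**Size of the misreading.** If the whole arm cost is additional, the true cost per added point exceeds the average ratio by the factor S / (S − U):

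| Assumed U | Gain S − U | Factor |
|---|---|---|
| 30% | 25 | 55 / 25 = 2.2 |
| 40% | 15 | 55 / 15 = 3.7 |
| 45% | 10 | 55 / 10 = 5.5 |
| 50% | 5 | 55 / 5 = 11 |
| 55% | 0 | undefined |

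**Sensitivity to the cost assumption.** The cost model also counts nurse visits, some of which would occur without any product. If only a share f of the arm cost is additional, each factor is multiplied by f. At f = 0.5 the factors are 1.1, 1.8, 2.75 and 5.5. The average ratio understates as long as f exceeds (S − U) / S, which is 0.45, 0.27, 0.18 and 0.09 for the four rows.

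**If 45% is the ulcer-free rate.** Then S = 45, and with f = 1 the factor is 45 / 15 = 3 at U = 30% and 45 / 5 = 9 at U = 40%.

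**The case against.** The best defence is that the sentence refers to the planned values together. They include both between-arm differences and the incremental ratio, which is a genuine cost per additional point. The cost model also says that the incidence percentages feed the incremental estimations. So a reader might infer that the plan equates the average ratio alone with the cost of 1%, but the text does not say so. This part of the defence stands. It does not rescue the per-product wording, because the incremental ratio belongs to the pair of products and not to either one.

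A reader might also infer that the product with the lower average ratio will be declared the winner, since the Abstract says that "this research is intended to find the most cost-effective treatment". That is motivation. It names no ratio, and no section sets such a rule. One can show that, with total cost assumed at half of HOFA's and olive oil truly 10 points worse, olive oil would have the lower average ratio in practically every trial of 306 per arm. But the protocol's main conclusion rests on noninferiority, and an upper 95% limit below 10 points is reached in only about 2.5% of such trials. The ranking result therefore does not describe what this plan would conclude.

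Nor can the average ratio be called favourable to a useless product. It is finite, but without prices or a threshold nothing makes it favourable.

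Finally, both differences are already planned, and the absolute risk reduction gets a 95% confidence interval. That is correct, and it is why the remedy is small.

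**Conclusion.** The point holds as a defect in a stated output of the secondary objective. The protocol promises a cost per 1% gain for each product, its two active arms cannot estimate that, and the only per-product ratio in the plan is an average cost. That conclusion follows from the design and needs no numerical assumption.

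The size does depend on assumptions: 2.2 to 11 times understatement if 45% is the ulcer rate, if 30% to 50% would stay ulcer-free without a product, and if the whole arm cost is additional. With a smaller additional share of cost the factor shrinks in proportion. The primary endpoint, the noninferiority test and the sample size are unaffected.

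**What to change.** In the cost-effectiveness paragraph of Statistical analysis:

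- Remove the per-product ending ("in these patients by using each product") and state that any cost per 1% of success refers to olive oil relative to HOFA.
- Refer to one incremental ratio, olive oil versus HOFA, in place of one for each option.
- Base the cost-effectiveness conclusion on the between-arm differences in mean cost and in ulcer incidence, each with a confidence interval. These remain interpretable when the effect difference is near zero, which is the planning assumption and where the incremental ratio breaks down.
- If the per-arm ratio is kept, label it mean cost per ulcer-free patient in that arm (mean cost divided by the ulcer-free proportion) and state that it is not a marginal cost.

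This needs no new data, visits or patients. The only loss is a per-product headline figure that the design cannot support.
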